#### Trial monitoring

The steering committee consists of the chief investigator, site investigators, and an academic investigator who contributed to the design and revision of the study protocol. The chief investigator is responsible for the study administrative management, communication with local investigators, and assists participating centres with trial conduct, record keeping, and data management. A planned interim analysis 1 year into trial, or at *n* = 50, whichever occurs first, will consider trial conduct, recruitment, adverse events, and adherence to trial protocol. The volume and duration of provided physiotherapy will be compared between groups. The trial will be amended or ceased due to futility if there are critical failures to recruitment rates, breaches to protocol, or minimal treatment separation between groups. Primary or secondary outcome differences will not be investigated at this interim analysis as this could lead to a subconscious bias in trial conduct.

### Ethics and dissemination

#### Retrospective consent

Ethics approval has been granted for eligible patients to be randomised prior to consent. Patients within the first two postoperative days after emergency abdominal surgery are often unwell and in an emotionally vulnerable state. Initial ethics approval was granted with a traditional enrolment into the trial following gaining of consent. However, following a planned interim analysis of trial conduct on the 50th patient recruited into the trial (unpublished data), patients and next of kin reported feeling distressed when approached by researchers in the first two postoperative days to discuss the trial. Further detailed feedback on the consenting process was sought from patients (*n* = 20) at 1-week post-surgery. All patients reported feeling too unwell in the first few days after surgery and disliked having to consider participating in a trial that was comparing two forms of low-risk commonly provided care. All patients indicated that they would prefer to provide retrospective consent. They recommended approximately no earlier than the third postoperative day or when they were not feeling nauseated. The two comparison interventions had nil documented occasions of harm at that point in the trial. Adverse events are similarly very low (< 1%) in critically unwell patients who are provided with 30 min of daily rehabilitation therapy [25]. There is minimal clinical risk to the patient being provided with either two arms of the study. Randomisation immediately on eligibility also allows the physiotherapy protocol to be delivered without delay, possibly enhancing the clinical outcome for all participants. Additionally, the primary outcome measure is non-invasive, has minimal risk, and requires no additional participation from the patient outside of standard care. An application to all responsible ethics committees was placed to alter consent to a retrospective consent following randomisation and was granted.

The principal site investigator will approach the patient from the fourth postoperative day and describe the trial, including the potential risks and benefits, and involvement required from the patient. Written information will be provided, and the patient will be invited to participate in the trial. Any person not consenting following randomisation is withdrawn from the trial. If the patient consents to continue in the trial, they will sign a consent form as required by local ethics committees and in accordance with the Declaration of Helsinki. If the patient remains in a state where informed consent is unable to be provided, (i.e. unconscious, delirious, nauseated, pain, repeat surgery) the next of kin will be contacted for consent. If the patient or next of kin declines to participate, the patient will take no further part in the trial and all data will be withdrawn. Physiotherapy will then be provided to them at the discretion of the ward physiotherapist.

Trial participants will have the autonomy to decline any therapy session as per standard care provision and medico-legal requirements regardless of recruitment into the trial. Reasons for non-participation in therapy sessions will be documented.

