### Trial design

ICEAGE is a pragmatic, multicentre, parallel-group, randomised controlled trial. It is patient and assessor blinded, and powered for superiority. Eligible patients will be randomly assigned via concealed allocation into one of two physiotherapy treatment arms (Table 1). The control group will receive standard care physiotherapy from the first postoperative day consisting of education on prevention of complications with upright positioning, ambulation, and breathing exercises; a single deep breathing and coughing (DB&C) coaching session; and no more than 15 min of supervised ambulation once daily until a threshold score is met to discharge from this service. The intervention group will receive an enhanced physiotherapy care package from the first postoperative day consisting of (i) education on prevention of complications with upright positioning, ambulation, and breathing exercises; (ii) at least twice daily coached DB&C for the first two postoperative days; and (iii) at least 30 min of supervised early rehabilitation daily for the first five postoperative days. The mode of ambulation and respiratory physiotherapy will be standardised for both groups. The difference between groups will be (1) additional reminders and education as necessary for performance of independent exercises, (2) longer duration of ambulation and/or provision of individualised rehabilitation exercises, and (3) increased number of coached DB&C sessions (see Fig. 1 for the ICEAGE trial CONSORT diagram).

**Table 1 Tab1:** TIDieR descriptions of ICEAGE interventions

TIDieR criterion	Control	Intervention
Item 1. Brief name: provide the name or a phrase that describes the intervention	Standard care: ‘talk, walk, breathe’	Enhanced physiotherapy care: ‘talk more, exercise more, breathe more’

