### Eligibility and exclusion criteria

Local investigators will screen daily surgery lists and recruit eligible patients from the ICU and wards at participating hospitals. Eligible patients will be adults over 18 years having open emergency abdominal surgery. This is defined as time-critical surgery (within 48 h of decision to operate) for a condition that is an immediate or intermediate threat to life or organ survival, involving at least one incision greater than, or equal to, 5 cm anywhere in the abdomen and through the fascia, for an existing hospital patient or a person admitted through the emergency department and requiring at least an overnight stay. Exclusion criteria are as follows: procedures solely involving inguinal hernia repairs, appendectomies, organ transplantation, thoracic, or gynaecological surgery; a PPC diagnosis anytime in the 24 h prior to eligibility screening; a pre-existing condition where the patient is unable to stand upright and ambulate for 1 min without a seated rest; severe cognitive impairment; unable to understand spoken English without the assistance of an interpreter (as determined by the research assistant, site investigator or ward physiotherapist performing eligibility screening); within 7 days of elective abdominal surgery; planned repeat surgery within 5 days of emergency procedure; approaching imminent death or withdrawal of medical treatment within 48 h of their surgical procedure; medical orders not to participate in early active rehabilitation; patients unable to be randomised by the research team within 48 h of surgery; enrolment in another clinical trial with similar endpoints; and previous enrolment in ICEAGE.

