### Trial withdrawal

A patient is withdrawn if they withdraw their consent or do not provide consent following randomisation.

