##### Secondary outcomes

Binomial outcomes including rehabilitation referrals, pneumonia, PPOI, unplanned ICU admissions, patient-reported complications, and mortality will be analysed using multivariate robust random effects Poisson generalised linear regression.Time-to-event binomial outcomes (e.g. PPC, pneumonia, PPOI, achievement of ambulation goals of 1 and 10 min; and hospital and ICU LOS; and mortality) will be compared by estimating hazard ratios using Cox proportional hazards regression, with and without covariate adjustment where necessary and graphically illustrated using Kaplan-Meier methods.Measures involving estimation of rate of change over time (QOL and functional capacity) will be analysed using repeated-measures mixed effects linear regression or ordered logistic regression for rank-ordered scale measures.Hospital costs will be compared using mixed effects linear regression. Log transformation of highly skewed cost data will be performed. Depending on the adequacy of the data for purposes of economic analysis, a cost-utility may be conducted.

All outcomes will be analysed on an intention-to-treat basis. An intention-to-protocol sensitivity analysis will be performed by identifying as a separate group participants who received more than 80% of planned protocol sessions as per group allocation. Other planned sensitivity analyses will be made according to age (> 65), surgery type (colorectal, upper gastrointestinal, other), preoperative self-reported physical capacity, and gender. Sensitivity of outcome estimates to missing data will be evaluated using multiple imputations. All analyses will be performed using Stata MP2 V14 (StataCorp, College Station, TX, USA).

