## Discussion

ICEAGE will provide the first high-level degree of evidence for the possible benefit of physiotherapy to reduce complications and improve physical recovery following emergency abdominal surgery. This trial involves three different types of hospitals: rural, regional, and metropolitan; includes most types of open major emergency abdominal surgery; and is conducted within a pragmatic framework where all other perioperative care is conducted without change. Our findings will be highly generalizable to most first-world hospitals.

In keeping with normal clinical practice and pragmatic trial methodology, it is unlikely that the interventions will be provided exactly as per protocol for every planned session; indeed, there will be many occasions where it will not be possible to treat a patient as planned due to extraneous circumstances (e.g. away at imaging, returned to theatre, refuses treatment, sudden deterioration). To ensure that our findings are relevant to practical real-life clinical situations in which our interventions are intended to be applied in, all patients entered in the trial will be analysed according to intention-to-treat principles, regardless of adherence to protocol. To determine if results are affected by adherence, we have planned a per-protocol sensitivity analysis of those patients who adhered to the protocol in more than 80% of intended occasions.

All assessors and patients will be masked to group allocation, and there is an active-placebo of current practice physiotherapy. This will ensure that any effects are independently associated with the additional therapy provided rather than the Hawthorne effect of health professional interaction. ICEAGE will include not only short-term clinical outcomes, but medium-term patient-reported QOL and physical recovery, and long-term mortality. The results of ICEAGE will inform the clinical provision of physiotherapy to millions of patients globally every year.

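### Patients randomised before consent lose all their data if they decline, yet the analysis is called intention-to-treat of everyone entered

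*Protocol article*

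**What the plan says.** Protocol article, Retrospective consent: "Ethics approval has been granted for eligible patients to be randomised prior to consent". The same section explains that enrolment first followed consent, and that the change came after a conduct review at the 50th patient. Eligibility and exclusion criteria rules out "patients unable to be randomised by the research team within 48 h of surgery", so randomisation comes early.

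On the consent approach, Retrospective consent says: "The principal site investigator will approach the patient from the fourth postoperative day". If the patient or next of kin declines, "the patient will take no further part in the trial and all data will be withdrawn". Trial withdrawal agrees: "A patient is withdrawn if they withdraw their consent or do not provide consent following randomisation".

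On the analysis set, Statistical methods, under Secondary outcomes, says: "All outcomes will be analysed on an intention-to-treat basis". The Discussion goes further: "all patients entered in the trial will be analysed according to intention-to-treat principles, regardless of adherence to protocol". Neither place makes an exception for patients who decline after randomisation. The missing-data plan is multiple imputation as a sensitivity analysis.

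**The concern.** Intention-to-treat protects the comparison because every randomised patient is counted in the allocated arm. Here a patient can leave the analysis after allocation, after most of the treatment and possibly after the primary event. The two rules are stated in the same article with nothing to reconcile them, and a separate analysis plan could not recover data that have been withdrawn.

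At stake is the primary comparison. If willingness to consent depends on the regimen experienced and on how the patient fared, the PPC risk ratio among consenters is biased, in either direction. If it does not, the label is still wrong and readers cannot judge the risk, because the article sets out no analysis that accounts for the decliners.

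**Working it through.** **1. What has happened by the time consent is sought.**

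| Item | Source | Position at postoperative day 4 |
|---|---|---|
| Randomisation | Eligibility and exclusion criteria: within 48 h of surgery | done |
| Breathing component, intervention arm | Trial design: "at least twice daily coached DB&C for the first two postoperative days" | complete, if delivered as planned |
| Rehabilitation, intervention arm | Trial design: first five postoperative days | about 3 to 4 of 5 days |
| Primary outcome | Primary outcome: first 14 postoperative hospital days | early PPCs may already have occurred |

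So the consent decision can follow both exposure and outcome.

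**2. The plan's own sample size reproduces and is not the fault.** For 20% v 8%, two-sided 0.05, 80% power, pooled variance, no continuity correction:

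n = [1.96 × √(2 × 0.14 × 0.86) + 0.8416 × √(0.16 + 0.0736)]² / 0.12² = (0.962 + 0.407)² / 0.0144 ≈ 130.1, rounded up to 131 per arm, 262 in total, as stated.

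Power with all 288 retained is 83.9%. If refusals remove 5%, 10%, 15% or 20%, it is 82.0%, 79.9%, 77.5% or 75.0%. The loss of power is small; selection is the issue.

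**3. Bias with no true effect (20% PPC in both arms).** The article gives no refusal rate, so every refusal figure here is an assumption. If a fraction d of an arm declines and decliners have PPC risk q, the observed risk among consenters is (0.20 − d × q) / (1 − d).

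- Control, d = 0.10, q = 0.20: (0.20 − 0.02) / 0.90 = 0.200.
- Intervention, d = 0.10, q = 0.40: (0.20 − 0.04) / 0.90 = 0.178.
- Observed risk ratio: 0.178 / 0.200 = 0.89. The chance of a false significant result is about 7.4% instead of 5%.

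If about 50 of the 288 consented beforehand, 238 are exposed and 10% refusal among them is 0.10 × 238 / 288 = 8.3% of the arm. Then (0.20 − 0.083 × 0.40) / 0.917 = 0.182, a risk ratio of 0.91.

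The same calculation with refusal probability set by arm and PPC status, 144 per arm:

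| Control refusal (PPC / no PPC) | Intervention refusal (PPC / no PPC) | Observed risk ratio | False-positive rate |
|---|---|---|---|
| 10% / 10% | 10% / 10% | 1.00 | 5.0% |
| 20% / 10% | 20% / 10% | 1.00 | 5.0% |
| 5% / 5% | 20% / 10% | 0.91 | 6.6% |
| 5% / 5% | 30% / 5% | 0.78 | 15.6% |
| 10% / 10% | 40% / 10% | 0.71 | 22% |

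In these scenarios bias appears only when refusal depends on arm and outcome together. Swapping the arms would push the risk ratio above 1.

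**4. What a count-only sensitivity analysis would show.** Take a result near the design values, 10/130 v 26/130 (7.7% v 20%; risk ratio 0.38; chi-square without correction, p = 0.004), and add back an assumed 14 decliners per arm.

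- Worst case, 14 v 0 PPCs: 24/144 v 26/144, risk ratio 0.92, p = 0.76.
- Best case, 0 v 14: 10/144 v 40/144, risk ratio 0.25.
- Tipping point with 3 PPCs among control decliners: 5 among intervention decliners gives p = 0.022, 6 gives p = 0.035, and 7 gives 17/144 v 29/144, risk ratio 0.59, p = 0.054.

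Crossing 0.05 here therefore needs 7/14 = 50% PPC in intervention decliners, against 7.7% in intervention consenters. Only the number of decliners per arm is needed to run this.

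**The case against.** The other side has substance.

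- **Selective refusal is not shown.** A reader might infer that exclusions do depend on arm and early course. The article documents only that they could. All 20 patients consulted preferred retrospective consent, and both arms receive physiotherapy so that patients are expected to be blind to allocation. This lowers the risk. It does not remove it: the arms differ in session length and number, blinding is only anticipated, and the check is a guess from 30 participants at the 90-day interview.
- **The sickest are not removed as a class.** A reader might infer that incapacitated or deceased patients are dropped. The section gives a next-of-kin route for those unable to consent, does not mention deaths, and withdraws data only on refusal.
- **The plan's 10% is not a refusal rate.** It covers dropout and withdrawal, within an increase that also allows for uncertainty in incidence and effect. Assigning all of it to refusals is an assumption.
- **Part of the sample is unaffected.** Roughly the first 50 patients consented before enrolment.
- **Unmasked consent-taking is not established.** Randomisation and allocation lets the site investigator keep opened envelopes, while the Primary outcome section describes a blinded site investigator. These need reconciling; they do not prove that the person seeking consent knew the arm.
- **Withdrawal may be an ethics condition**, and the commitment to CONSORT reporting already implies counts of withdrawals by arm.

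All of this limits how strongly the risk may be put. None of it reconciles the withdrawal rule with the intention-to-treat statements. Imputation needs retained records, and the planned comparison of included and excluded patients uses demographics and planned procedure, not outcome by arm.

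**Conclusion.** The contradiction stands. For patients enrolled under retrospective consent, analysis of everyone randomised cannot be done once one person declines, and the article states no alternative set. If nobody declines, no harm follows.

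The size of any bias is unknown, because no refusal rate is given. Under the assumed illustrations with no true effect, the risk ratio runs from 1.00, when refusal is unrelated to arm, through 0.89 in the 10% example, to 0.71 in the most extreme scenario tried. A reader might conclude that a significant result would be overturned. The documents do not support that: the one example that moves p to 0.054 rests on an assumed 50% PPC rate in intervention decliners. What is supported is that the label is wrong as written, and that the planned analyses described leave the effect of post-randomisation refusal on the primary result unexamined.

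**What to change.** 1. In Statistical methods and in the Discussion, call the primary analysis set randomised and consented (modified intention-to-treat). Report the number and timing of post-randomisation non-consents by arm, taken from the numbered envelope log.
2. Add best/worst-case and tipping-point analyses of PPC that add the decliners back by arm, using counts only.
3. Reconcile Randomisation and allocation (site investigator may hold opened envelopes) with Primary outcome (blinded site investigator), so that the person seeking consent has no access to allocation.

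Optionally, ask the ethics committees whether routinely recorded PPC and vital status of decliners may be retained. This is data retention that needs approval, not a wording change. With recruitment expected to end in late 2018, it and item 3 may reach few remaining participants.

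The cost of items 1 and 2 is a less favourable label and a short extra analysis; item 3 is a change to who holds the envelopes or who asks for consent.

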#### Dissemination

This protocol is reported according to the SPIRIT guideline [37]. Trial results will be written in accordance with the CONSORT extensions for a pragmatic trial using a non-pharmacological intervention, published in a peer-reviewed journal, and presented at national and international meetings.

#### Trial status

This trial is currently active. First participant was recruited on 25 June 2015. It is anticipated that recruitment will be completed in late 2018.

## Discussion

ICEAGE will provide the first high-level degree of evidence for the possible benefit of physiotherapy to reduce complications and improve physical recovery following emergency abdominal surgery. This trial involves three different types of hospitals: rural, regional, and metropolitan; includes most types of open major emergency abdominal surgery; and is conducted within a pragmatic framework where all other perioperative care is conducted without change. Our findings will be highly generalizable to most first-world hospitals.

In keeping with normal clinical practice and pragmatic trial methodology, it is unlikely that the interventions will be provided exactly as per protocol for every planned session; indeed, there will be many occasions where it will not be possible to treat a patient as planned due to extraneous circumstances (e.g. away at imaging, returned to theatre, refuses treatment, sudden deterioration). To ensure that our findings are relevant to practical real-life clinical situations in which our interventions are intended to be applied in, all patients entered in the trial will be analysed according to intention-to-treat principles, regardless of adherence to protocol. To determine if results are affected by adherence, we have planned a per-protocol sensitivity analysis of those patients who adhered to the protocol in more than 80% of intended occasions.

All assessors and patients will be masked to group allocation, and there is an active-placebo of current practice physiotherapy. This will ensure that any effects are independently associated with the additional therapy provided rather than the Hawthorne effect of health professional interaction. ICEAGE will include not only short-term clinical outcomes, but medium-term patient-reported QOL and physical recovery, and long-term mortality. The results of ICEAGE will inform the clinical provision of physiotherapy to millions of patients globally every year.

## Abbreviations

CRF: Case report form
CXR: Chest X-ray
DB&C: Deep breathing and coughing
EQ-5D: EuroQual five domains
ICEAGE: Incidence of Complications following Emergency Abdominal surgery—Get Exercising
ICU: Intensive care unit
LOS: Length of stay
mILOA: Modified Iowa level of assistance
PPC: Postoperative pulmonary complication
PPOI: Prolonged postoperative ileus
QOL: Quality of life
SAE: Serious adverse event
SAQ: Self-administered physical activity questionnaire
SOFA: Sequential organ failure assessment
VAS: Visual analogue scale
WHODAS: World Health Organisation disability assessment score
